## Methods and analysis

### Study population

This prospective cohort study, will enroll over 4000 individuals with RT-PCR-confirmedSARS-CoV-2 at baseline, hospitalized at Gansu Provincial Hospital in China from December 2022 to May 2023 (Gansu PASC dataset). Aligning with methodologies from other PASC research, we will gather comprehensive health data during the patients’ initial hospitalization due to COVID-19 (31). The data collection will include extensive hospital records from their acute COVID-19 admissions, capturing demographic information, clinical data, comorbidities, pre-existing symptoms, and other relevant health details.

The patients were from all 14 cities in Gansu Province (92°13′E-108°46′E, 32°31’N-42°57’N), with various environmental and socioeconomic backgrounds. The municipal geographic coordinates of the 14 cities are detailed as follows: Lanzhou (103°51′E, 36°3’N); Jiayuguan (98°23′E, 39°80’N); Jinchang (102°19′E, 38°52’N); Baiyin (104°14′E, 36°55’N); Tianshui (105°72′E, 34°58’N); Wuwei (102°64′E, 37°93’N); Zhangye (100°45′E, 38°92’N); Pingliang (106°66′E, 35°54’N); Jiuquan (98°49′E, 39°73’N); Qingyang (107°64′E, 35°71’N); Dingxi (104°59′E, 35°61’N); Longnan (104°96′E, 33°37’N); Linxia Hui Autonomous Prefecture (103°21′E, 35°60’N) and Gannan Zang Autonomous Prefecture (102°91′E, 34°98’N). Baseline data will be collected using hospital records, and follow-up assessments will be performed at 24-, 36-, and 48-months post-discharge via structured telephone interviews (Table 1). Exclusion criteria are limited to individuals without available contact details, those who deceased during hospitalization or follow-up, those who declined to participate, and those unreachable for follow-up assessments.

**Table 1 tab1:** Evaluation parameters at baseline and follow-up visits.

Evaluation parameter	Baseline°	Follow-Up°° (telephone interviews)		
	(Hospital admission)	Visit 1 (24 m)	Visit 2 (36 m)	Visit 3 (48 m)
Informed consent	x			
Inclusion criteria met	x			
Demographics*	x			
Environmental/socio-economic factors†	x			
Symptoms‡	x	x	x	x
Life styles¶	x	x	x	x
Vaccination information**	x			
Reinfection††		x	x	x
Recovery condition‡‡		x	x	x
Comorbidities¶¶	x			
Laboratory test results***	x			
Treatment†††	x			
Clinical outcomes	x			
Medical management‡‡‡		x	x	x
Assessment Tools¶¶¶				
EQ-5D-5L score (Adults)	x	x	x	x
mMRC score (Adults)	x	x	x	x
GAD-7 score (Adults)	x	x	x	x
PHQ-9 score (Adults)	x	x	x	x
FSS score (Adults)	x	x	x	x

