#### Socioeconomic data

Socioeconomic data including city-level per capita, income levels, employment status, job types, education level, and living conditions will be collected during follow-up visits and sourced from the Gansu Development Yearbook, published by the Gansu Province Bureau of Statistic.

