### Statistical analysis

A variety of statistical methodologies will be employed to analyze the primary and secondary outcomes in this study. The data analysis begins with descriptive and inferential statistical methods to identify patterns and establish correlations. Continuous data will be presented as means with standard deviations (SD), while categorical variables will be reported as percentages. For comparisons across groups, analysis of variance (ANOVA) will be used for continuous variables, and chi-square tests for categorical variables, both with Bonferroni corrections applied in post-hoc analyses. A significance level of *p* < 0.05 will be consistently applied, with adjustments made for multiple comparisons to enhance the reliability of results. Logistic regression models will be employed to evaluate the impact of multiple factors on the severity of PASC. We will utilize a multivariable logistic regression model to analyze the relationship between various independent variables, including demographic factors, clinical characteristics, and environmental exposures, and the binary outcome of PASC presence or absence. The model will integrate variables selected based on clinical relevance and statistical significance derived from preliminary univariate analyses, ensuring that only factors significantly associated with the outcome are included in the final analysis. Variables for inclusion will be chosen based on their potential impact on PASC, informed by both clinical judgment and empirical evidence from initial analyses. We plan to investigate interaction terms, particularly between key demographic and clinical variables, to explore complex interactions that may affect PASC risk. Model fit will be assessed using the Hosmer-Lemeshow test for goodness-of-fit and Receiver Operating Characteristic curve analysis to evaluate predictive accuracy. We will also employ validation techniques such as split-sample validation or cross-validation to confirm the model’s robustness. Sensitivity analyses will be conducted to examine the stability of our results under various assumptions regarding data missingness and potential measurement errors, ensuring that our findings are reliable and applicable across different scenarios. Additionally, advanced analytical techniques will complement these methods, utilizing R (version 4.3.0) with the ‘gpboost’ and ‘stats’ packages and Python (version 3.10) with ‘sklearn’ and ‘gpboost.’

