#### Generalized linear mixed-effects models (GLMM) for risk factor estimation

To estimate the influence of risk factors on PASC, Generalized Linear Mixed-Effects Models (GLMM) will be applied. These models will allow for a quantitative assessment of how various environmental and individual-level risk factors contribute to PASC, while controlling for potential confounders. A random intercept for each city will be included to account for non-measurable inter-city variability. Interaction terms between individual and environmental factors will be constructed, with only those demonstrating statistical significance and theoretical or empirical relevance retained for further analysis.

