Despite the strengths of our study, we acknowledge several limitations and have devised strategies to address them effectively. Firstly, our study is based in Gansu Province, China, involving data from 14 cities, each with unique environmental and socioeconomic characteristics. While this provides a rich dataset within a specific geographic region, it limits broader geographic representation. To address this, we have included multiple sites chosen for their environmental diversity, particularly focusing on urban settings across different regions. This strategic selection helps control environmental factors that could influence health outcomes related to PASC. Secondly, our current study setup does not include direct comparisons with other cities or countries, which restricts our ability to generalize findings across different global environments. We plan to expand our analysis to include such comparisons as comparable data becomes available, allowing for a more comprehensive evaluation of environmental and socioeconomic impacts on PASC rates and health outcomes. Thirdly, the non-random nature of our patient recruitment might introduce selection bias, and the reliance on telephone questionnaires could lead to recall bias, particularly as participants may not accurately remember past symptoms. To mitigate these issues, we use advanced statistical methods to control for potential confounders and perform sensitivity analyses to assess the impact of data attrition. Fourthly, an oversight committee is actively involved in monitoring and evaluating the study’s processes to address any unforeseen issues that arise, thereby ensuring the integrity and validity of our research. Plans for further validation through clinical assessments are in place to enhance the reliability of our findings, particularly to address challenges associated with self-reported data. By implementing these strategies, we aim to refine our understanding of PASC and its diverse impacts across different populations, ensuring that our findings are robust and reflective of the true effects of environmental and socioeconomic factors on health outcomes post-COVID-19.

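### Two models cover the same environmental factors, one ignoring and one allowing for the 14 cities, and the protocol does not say which governs inference

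*Protocol article*

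**What the plan says.** The opening paragraph of the protocol article's Statistical analysis section commits to a fixed-effects model for PASC yes or no: "We will utilize a multivariable logistic regression model to analyze the relationship between various independent variables, including demographic factors, clinical characteristics, and environmental exposures". Variables enter on clinical relevance and on "statistical significance derived from preliminary univariate analyses, ensuring that only factors significantly associated with the outcome are included in the final analysis". The 0.05 level "will be consistently applied, with adjustments made for multiple comparisons to enhance the reliability of results". Neither the model nor the screen mentions city. The same paragraph presents the advanced techniques as an addition to these methods, not as their replacement.

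The next subsection, on generalized linear mixed-effects models (GLMM), starts again on the same task: "To estimate the influence of risk factors on PASC, Generalized Linear Mixed-Effects Models (GLMM) will be applied". It names environmental as well as individual-level factors and adds: "A random intercept for each city will be included to account for non-measurable inter-city variability".

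On the data, Study population says "The patients were from all 14 cities in Gansu Province", all of them treated at one hospital. The Socioeconomic data section opens with "Socioeconomic data including city-level per capita" and draws partly on a provincial yearbook. Environmental data matches pollutants, weather and vegetation index to each patient's location and admission period.

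**The concern.** Patients from one city share yearbook values exactly and share much of their climate, vegetation and pollution. If PASC frequency also differs between cities for unmeasured reasons, 4,000 patients carry far less information about such factors than 4,000 independent ones. A logistic model without a city term then gives standard errors that are too small. Adjusting for multiple comparisons does not repair this, because each p-value is already wrong before adjustment.

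Two consequences follow from the text. The same exposure can be significant in the logistic model and not in the GLMM, and either result could be reported. The un-clustered screen also decides which factors reach the logistic model's final form. Quantifying environmental and socioeconomic influences is the study's declared purpose, so this bears on its main conclusions.

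**Working it through.** The protocol gives no power calculation or ICC, so there is no stated figure to reproduce other than the nominal 5%, which the formula below returns when the ICC is 0.

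**Inputs.** From the documents: 4,000 patients (the text says over 4,000), 14 cities, alpha 0.05. Assumed: two-sided tests; ICC from 0.001 to 0.05; PASC frequency 30% (simulation only). The split of patients by city is not given.

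**Formula.** Patients per city m = 4000/14 = 285.7. Design effect DE = 1 + (m − 1) × ICC × r, where r is the within-city correlation of the covariate (1 if constant within city). Actual type I error of a test assuming independence = 2 × [1 − Φ(1.96/√DE)].

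Example with r = 1 and ICC 0.005: DE = 1 + 284.7 × 0.005 = 2.42, √DE = 1.56, 1.96/1.56 = 1.26, error 20.8%.

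| ICC | DE (r = 1) | Error, r = 1 | Error, r = 0.5 | Error, r = 0.1 |
|---|---|---|---|---|
| 0.001 | 1.28 | 8.4% | 6.7% | 5.3% |
| 0.002 | 1.57 | 11.8% | 8.4% | 5.7% |
| 0.005 | 2.42 | 20.8% | 13.4% | 6.7% |
| 0.01 | 3.85 | 31.8% | 20.8% | 8.4% |
| 0.02 | 6.69 | 44.9% | 31.8% | 11.8% |
| 0.05 | 15.24 | 61.6% | 49.2% | 20.8% |

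**Simulation.** 14 cities, a null city-level covariate and 1,500 replicates per setting. City sizes were either equal (286 each) or unequal (one city of 2,000, thirteen of 154). The random-intercept model was approximated by maximum likelihood on city empirical logits. Each cell shows equal / unequal sizes.

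| ICC | Plain logistic | Random intercept, z | Random intercept, t on 12 df |
|---|---|---|---|
| 0 | 5.5% / 4.0% | 4.8% / 3.9% | 2.4% / 1.9% |
| 0.002 | 9.7% / 12.0% | 7.1% / 9.0% | 4.9% / 6.5% |
| 0.005 | 14.8% / 21.7% | 7.5% / 11.3% | 6.0% / 8.2% |
| 0.01 | 24.3% / 32.2% | 8.1% / 10.8% | 5.7% / 8.0% |
| 0.02 | 37.3% / 40.5% | 9.8% / 9.0% | 6.7% / 6.5% |
| 0.05 | 56.5% / 57.7% | 9.5% / 9.1% | 6.8% / 6.5% |

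The equal-size results lie below the formula because the simulated ICC is on the latent logistic scale. On the observed scale it is about (π²/3) × 0.3 × 0.7 = 0.69 times as large. Putting 0.69 × 0.01 = 0.0069 into the formula gives DE 2.96 and 25.5%, against 24.3% simulated. Simulation error is about 0.7 percentage points near 8% (√(0.08 × 0.92/1500)).

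**Small number of cities.** With one city-level covariate, 14 − 1 − 1 = 12 df remain, and P(|t| > 1.96) = 7.4%. With five, 8 df remain and it is 8.6%.

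**The case against.** A reader might infer that environmental effects are tested only in a plain logistic regression and that false-positive rates are therefore several times 5%. The documents do not support that. The GLMM subsection is the one devoted to estimating risk factors, it covers environmental factors, and it has the city intercept. The abstract and the Discussion name mixed-effects models for this purpose and do not mention logistic regression. Feature elimination for the boosting model relies on the GLMM. Nothing says that the GLMM takes its variables from the univariate screen, and entry to the logistic model also rests on clinical relevance.

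The large error rates belong to the extreme case. Environmental exposures are matched to each patient's location and admission period, with pollutants and vegetation index on a 1 km grid and monthly weather on a 0.25° grid. Admissions run from December to May, so many exposures vary within city. Some socioeconomic items come from the patients themselves. The sentence that lists the logistic predictors names environmental exposures, not yearbook variables. At r = 0.1 and ICC 0.005–0.01, the error is only 6.7–8.4%.

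Two further inferences go beyond the text. The protocol does not say that the GLMM will use a Wald z test. That patients from distant cities are a selected, referred group is plausible with one hospital, but is not stated.

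All of this narrows the point without removing it. The logistic model is a stated commitment, with its own significance level and entry rule, and no sentence ranks it below the GLMM. A fuller analysis plan may do so, but the article as it stands describes two competing analyses.

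**Conclusion.** The concern holds in limited form. The protocol sets out two analyses of the same environmental factors, one ignoring city and one modelling it, without saying which governs, and its univariate screen makes no stated allowance for city.

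For a factor constant within city, the plain logistic test has a type I error of about 8% at ICC 0.001, 10–12% at 0.002, 15–22% at 0.005, 24–32% at 0.01 and above 50% at 0.05. These figures rest on an assumed ICC and on a covariate that does not vary within city. They are upper values for exposures that differ by place or month, and it cannot be said from the documents that any particular factor will be falsely declared significant. The planned GLMM brings the error to about 7–11% with a z reference and 5–8% with t on 12 df, so the remedy is largely in the protocol already and needs to be made decisive.

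**What to change.** Amend the Statistical analysis section as follows.

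- State that inference on environmental and socioeconomic factors comes only from the GLMM with a city random intercept.
- For these factors, replace the un-clustered univariate screen with the same GLMM or with a prespecified list.
- Keep the plain logistic model for descriptive or predictive use.
- Test city-level covariates against t with df = 14 − 1 − (number of city-level covariates), or by a permutation test at city level.

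Residence-to-hospital distance, or local versus referred status, may be added as a sensitivity analysis. Whether to adjust for acute severity should be left to the planned causal diagrams: the Discussion links air pollution to COVID-19 severity, so severity may lie on the causal path.

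As a side correction, the limitations paragraph of the Discussion says "we have included multiple sites chosen for their environmental diversity, particularly focusing on urban settings across different regions". This should be reconciled with the single recruiting hospital in Study population.

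The cost is mainly wording; the core changes need no new data. Intervals for city-level factors will be wider, which reflects what 14 cities can support.

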‡‡Recovery Assessment: Includes a single question about recovery perception post-COVID-19, with responses categorized as yes, no, or unsure.

¶¶Comorbidities: Comprehensive data collection on conditions such as hypertension, various cardiovascular and respiratory diseases, diabetes, chronic liver and kidney diseases, metabolic disorders, nervous system diseases, psychiatric conditions, cancers, rheumatism, tuberculosis, and anemia, essential for assessing co-impact on health outcomes.

***Laboratory Test Results: Analysis of blood count, electrolytes, renal and liver functions, inflammatory markers, and coagulation profiles to provide a physiological snapshot of health impacts.

†††Treatment: Detailed record of all treatments administered, including medications, oxygen therapy, mechanical ventilation, ICU care, and other interventions, helping to correlate treatment strategies with outcomes.

‡‡‡Medical management: Information of visiting a doctor for any reason and treatment undertaken during follow-up.

¶¶¶Assessment Tools: Includes the 5-level EQ-5D version (EQ-5D-5L), The Modified Medical Research Council (mMRC) Dyspnea Scale, The Generalized Anxiety Disorder-7 (GAD-7), the Patient Health Questionnaire-9 (PHQ-9), The Fatigue Severity Scale (FSS), The Insomnia Severity Index (ISI), The EuroQol Five-Dimension Youth Questionnaire (EQ-5D-Y) assesses health-related quality of life, The Strengths and Difficulties Questionnaire (SDQ), The Patient-Reported Outcomes Measurement Information System (PROMIS).

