### Variables and data collection

#### Baseline variables

Individual baseline variables will be collected from the Gansu PASC dataset. We gather comprehensive health data during patients’ initial hospitalization for COVID-19. This baseline information serves as a reference to distinguish between pre-existing conditions and symptoms that may be attributed to PASC (41). These variables include demographic factors such as age, gender, ethnicity, marital status, educational background, employment status, and body mass index (BMI). Comorbidities recorded include hypertension, diabetes, respiratory diseases, liver diseases, and other relevant conditions. The Charlson Comorbidity Index (CCI) was adapted using a modified formula to assess morbidity and mortality risks. Conditions were scored as follows: one point for congestive heart failure, chronic pulmonary disease, diabetes, and other conditions; two points for chronic kidney disease and malignant neoplasms; three points for moderate to severe liver disease; and six points for Acquired Immunodeficiency Syndrome (AIDS) (42). Based on the CCI, comorbidities were categorized as mild (0–1), moderate (2–6), or severe (>6). Baseline laboratory assessments included complete blood counts, electrolyte panels, renal and liver function tests, inflammatory markers, and coagulation profiles. Initial treatment protocols involved various medications and supportive care measures, such as oxygen therapy, mechanical ventilation, and immunoglobulin treatments, with emergency interventions including tracheal intubation and cardiopulmonary resuscitation as required.

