## Discussion

This study will employ a longitudinal design to investigate how environmental, socioeconomic, and clinical factors shape PASC outcomes in a demographically diverse population. Comprehensive health data collected during the initial COVID-19 hospitalization help distinguish pre-existing conditions from symptoms emerging as part of PASC. By integrating these clinical records with environmental and socioeconomic variables through mixed-effects models and spatiotemporal analyses, the research provides a comprehensive understanding of how both internal factors (e.g., individual health status, comorbidities) and external factors (e.g., air quality, socioeconomic conditions) influence long-term health outcomes following COVID-19. To ensure a representative sample, the cohort is stratified by age, sex, and initial symptom severity, allowing for a detailed and subgroup-specific analysis of PASC manifestations. This multidimensional approach is essential for uncovering the complex interactions between patient-level susceptibility and broader external influences, ultimately informing targeted strategies to improve the management and mitigation of long-term COVID-19 effects.

Existing literature has widely documented the potential influences of underlying comorbidities, demographic factors, and environmental conditions on PASC outcomes (64). Pre-existing conditions such as cardiovascular disease, diabetes, and chronic respiratory disorders have been shown to exacerbate the severity of PASC symptoms, leading to prolonged recovery and an increased risk of complications (65). Individuals with chronic illnesses are more likely to experience severe acute COVID-19, which may predispose them to long-term sequelae due to sustained systemic inflammation and immune dysregulation (66). For instance, patients with diabetes and obesity have demonstrated heightened susceptibility to persistent inflammatory states post-COVID-19, contributing to ongoing fatigue, dyspnea, and cardiovascular dysfunction (67, 68). By examining how pre-existing health conditions interact with PASC, this study aims to elucidate the mechanisms through which chronic illnesses impact recovery trajectories and to identify potential intervention strategies.

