Beyond comorbidities, demographic factors such as gender, education level, and marital status may also influence PASC trajectories (69). Gender differences in immune response and health-seeking behaviors have been linked to variations in symptom persistence and severity, with women more frequently reporting prolonged PASC symptoms, including fatigue, neurological issues, and autonomic dysfunction (70). Additionally, education level and marital status serve as proxies for social support and healthcare access, both of which are critical for managing chronic conditions and facilitating recovery (71). Limited health literacy, often associated with lower education levels, may impact adherence to post-COVID care recommendations, while marital status may influence mental health resilience and access to medical resources (72–74). By incorporating these demographic variables into our analysis, we aim to identify groups with greater susceptibility or resilience to PASC and assess how these interactions affect recovery trajectories.

Environmental pressures, such as air quality, urbanization, and access to green spaces, are increasingly recognized as key determinants of post-COVID-19 health outcomes (15, 20, 75). Air pollution has been linked to increased COVID-19 severity and mortality, and higher exposure to PM2.5 and NO2 has been associated with a higher prevalence of long-term respiratory and cardiovascular symptoms in PASC patients (75). Conversely, access to green spaces has been shown to provide protective benefits, improving mental and respiratory health and facilitating recovery (76). Given the environmental diversity of our study sites, this research will assess how these factors contribute to symptom persistence and recovery, leveraging existing knowledge on environmental determinants of health outcomes to refine analytical approaches and enhance the understanding of PASC progression.

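### The regression models do not separate confounders from acute-phase variables, so comorbidity and pollution coefficients may be severity-adjusted direct effects read as overall impact

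*Protocol article*

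**What the plan says.** The Statistical analysis section of the protocol article plans a multivariable logistic model of "the relationship between various independent variables, including demographic factors, clinical characteristics, and environmental exposures, and the binary outcome of PASC presence or absence". Variables enter on clinical relevance and on univariate screening, "ensuring that only factors significantly associated with the outcome are included in the final analysis". The same section describes the aim as evaluating the impact of multiple factors.

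The GLMM section then sets out to assess "how various environmental and individual-level risk factors contribute to PASC, while controlling for potential confounders", with a random intercept for city. The GPBoost section removes features that the GLMM finds least significant, and ranks the rest by mean absolute SHAP value.

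The baseline is the COVID-19 admission itself. Under Baseline variables: "Baseline laboratory assessments included complete blood counts, electrolyte panels, renal and liver function tests, inflammatory markers, and coagulation profiles". The Treatment footnote to Table 1 adds: "Detailed record of all treatments administered, including medications, oxygen therapy, mechanical ventilation, ICU care, and other interventions".

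On mechanism, the Discussion says: "Individuals with chronic illnesses are more likely to experience severe acute COVID-19, which may predispose them to long-term sequelae". On the environment it says: "Air pollution has been linked to increased COVID-19 severity and mortality".

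A separate section on causal inference models plans DAGs, structural equation modeling (SEM) and propensity score matching.

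**The concern.** A variable that lies between an exposure and the outcome is not a confounder. Adjusting for it removes the part of the exposure's effect that passes through it. The article describes acute severity in that position for comorbidity, and gives the first link of the same route for air pollution. Its logistic model nevertheless takes clinical characteristics alongside upstream factors. The univariate screen favours whatever predicts PASC, and markers of acute severity are likely to do so.

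If they enter, coefficients in one table answer different questions. For ICU care or an inflammatory marker, the route through severity is still in the coefficient. For comorbidity or PM2.5, the coefficient is what remains with severity held fixed. Adjusting for severity can also induce bias if an unmeasured factor affects both severity and PASC.

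The error can carry forward. An upstream factor weakened by the adjustment may be eliminated before the GPBoost step, or may rank low on SHAP. Comorbidity and environment are among the factors that the study exists to quantify.

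**Working it through.** **Step 1. What the text fixes.**

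- Covariate classes: demographic, clinical and environmental together (Statistical analysis). The list is open-ended.
- Selection: clinical relevance plus univariate significance. There is no rule on causal order.
- Meaning of clinical characteristics: not defined. The Study population section lists clinical data separately from comorbidities, and Table 1 and Baseline variables place admission laboratory values and in-hospital treatment at baseline. Acute-phase variables are therefore eligible, but are not stated to be included.
- Route through severity: stated in full for chronic illness, and as a first link only for pollution.
- DAG: planned, to identify confounders, in a separate analysis. It is not tied to the logistic model or the GLMM.

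**Step 2. Size.** The article gives no effect size or PASC rate, so there is no figure to reproduce. All inputs below are assumptions.

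Let X be the upstream factor, M acute severity and Y PASC, with logistic links. For the 20%-risk rows, the risk of M when X = 0, and of Y when X = M = 0, is 0.20 (odds 0.25).

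- P(M=1 | X=1) = 0.25·OR_XM / (1 + 0.25·OR_XM)
- odds(Y | X, M) = 0.25 · OR_D^X · OR_MY^M
- P(Y | X) = Σ over M of P(Y | X, M)·P(M | X)
- Total OR = odds(Y | X=1) / odds(Y | X=0). The OR adjusted for M is OR_D.
- Share lost = 1 − ln(OR_D) / ln(total OR)

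Worked case, OR_XM 2, OR_MY 2, OR_D 1.3:

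- P(M) is 0.20 for X=0, and 0.5/1.5 = 0.3333 for X=1.
- X=0: 0.8×0.2000 + 0.2×0.3333 = 0.2267, odds 0.2931.
- X=1: odds 0.325 and 0.65 give risks 0.2453 and 0.3939. Then 0.6667×0.2453 + 0.3333×0.3939 = 0.2948, odds 0.4181.
- Total OR = 0.4181/0.2931 = 1.43. Share lost = 1 − 0.2624/0.3552 = 26%.

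| OR_XM / OR_MY / OR_D | Total OR | Adjusted OR | Log OR lost |
|---|---|---|---|
| 1.49 / 1.65 / 1.65 * | 1.70 | 1.65 | 5% |
| 1.2 / 2 / 1.1 | 1.12 | 1.10 | 18% |
| 2 / 2 / 1.3 | 1.43 | 1.30 | 26% |
| 2.23 / 2.46 / 1.22 * | 1.39 | 1.22 | 39% |
| 3 / 3 / 1.3 | 1.67 | 1.30 | 49% |
| 3.32 / 2.46 / 1.22 * | 1.51 | 1.22 | 52% |
| 3 / 3 / 1.0 | 1.30 | 1.00 | 100% |

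\* Logit intercepts −1.6 for M and −1.2 for Y (baseline risks 17% and 23%) in place of 20%; log ORs 0.4/0.5/0.5, 0.8/0.9/0.2 and 1.2/0.9/0.2.

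**Step 3. Is the direction certain?** No. With the 20% baseline risks:

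- Direct effect opposite in sign (2 / 2 / 0.7): total 0.78, adjusted 0.70. The protective effect looks larger.
- X unrelated to severity (1 / 3 / 1.5): total 1.47, adjusted 1.50. The odds ratio shifts slightly because it is not collapsible.
- Binary unmeasured cause (prevalence 40%, as for X), OR 3 on severity and 1/3 on PASC (2 / 1 / 1.3): total 1.29, adjusted 1.34.
- The same cause with OR 3 on both (2 / 2 / 1.3): total 1.39, adjusted 1.22, so 39% is lost.

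The last two lines were obtained by fitting both logistic models to the exact cell probabilities.

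**The case against.** The strongest reply is that the premise is inferred. Clinical characteristics could mean comorbidities or the Charlson index, and an article may leave the exact covariate list to a fuller document. The logistic model is checked by ROC curve, Hosmer-Lemeshow test and cross-validation, which suit a prediction model. The causal section plans SEM, a standard way to split direct from indirect effects. A severity-adjusted direct effect is also a legitimate estimand if it is labelled as one.

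Part of this stands. The text does not say that acute-phase variables will be in the model, so the consequence is conditional. However, the article does fix the covariate classes and a selection rule, and that rule would readily admit such variables. The text speaks of impact, influence and contribution as well as of prediction. The causal section does not commit SEM to a mediation analysis, and it draws its variables from prior assessments.

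A reader might infer more than the documents support:

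- **Every upstream factor is affected.** Vaccination and socioeconomic factors are not named in the model sentence, and no route through acute severity to PASC is stated for either.
- **The estimates condition on severity by design.** The Discussion does say that "the cohort is stratified by age, sex, and initial symptom severity", but in a sentence about representativeness and subgroup analysis. It does not show that the main estimates are adjusted for severity.
- **Effects will certainly be understated by about half, or even reversed.** Losses of that size need a weak direct effect with strong mediation. A reversal (for example, total OR 1.18 against about 0.92 adjusted) needed no direct effect plus an assumed unmeasured cause of both severity and PASC.

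**Conclusion.** The concern holds in conditional form, for comorbidity and environmental exposures. As written, the logistic model and the GLMM do not distinguish confounders from variables downstream of the exposure. If acute-phase variables enter, the coefficients for comorbidity and pollution are severity-adjusted direct effects and cannot be read as total effects.

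Attenuation is the likely result when direct and indirect paths agree, but it is not guaranteed. Its size cannot be stated from the document. The illustrative cases with agreeing paths and no unmeasured common cause run from about 5% of the log odds ratio to all of it, and every input to them is assumed.

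For pollution, the conclusion also requires joining two statements in the Discussion: pollution to severity, and severity to sequelae, the latter hedged and made in the context of chronic illness.

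**What to change.** In the Statistical analysis and GLMM sections:

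1. Choose the adjustment set for each main exposure (at least comorbidity and the environmental exposures) from the DAG already planned in the causal inference section, not from univariate significance.
2. Leave admission laboratory values, acute severity and in-hospital treatment out of the models meant to give total effects.
3. Report models that add those variables under a clear label: direct-effect or mediation (for example through the planned SEM), or prediction.
4. State that coefficients from an all-variable model, and SHAP ranks, are not comparable causal impacts.

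The cost is revised wording and a few more models and tables on data already collected. No new data are needed.
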